## Abstract

**Background:**

Tobacco use remains the leading cause of premature morbidity and mortality in the United States. Young adults are less successful at quitting, use cessation treatment less often than smokers of other ages, and can be a challenge to retain in treatment. Social media, integrated into the lives of many young adults, represents a promising strategy to deliver evidence-based smoking cessation treatment to a large, diverse audience. The goal of this trial is to test the efficacy of a stage-based smoking cessation intervention on Facebook for young adults age 18 to 25 on smoking abstinence, reduction in cigarettes smoked, and thoughts about smoking abstinence.

**Methods/Design:**

This is a randomized controlled trial. Young adult smokers throughout the United States are recruited online and randomized to either the 3 month Tobacco Status Project intervention on Facebook or a referral to a smoking cessation website. The intervention consists of assignment to a secret Facebook group tailored to readiness to quit smoking (precontemplation, contemplation, preparation), daily Facebook contacts tailored to readiness to quit smoking, weekly live counseling sessions, and for those in preparation, weekly Cognitive Behavioral Therapy counseling sessions on Facebook. Primary outcome measure is biochemically-verified 7-day point prevalence abstinence from smoking at posttreatment (3 months), 6, and 12 months. Secondary outcome measures are reduction of 50 % or more in cigarettes smoked, 24 h quit attempts, and commitment to abstinence at each time point. A secondary aim is to test, within the TSP condition, the effect of a monetary incentive at increasing engagement in the intervention.

**Discussion:**

This randomized controlled trial is testing a novel Facebook intervention for treating young adults’ tobacco use. If efficacious, the social media intervention could be disseminated widely and expanded to address additional health risks.

**Trial registration:**

ClinicalTrials.gov: NCT02207036, May 13, 2014.

## Background

Cigarette smoking is the single most important preventable cause of morbidity, mortality, and excess health cost in the United States (US), accounting for 480,000 premature deaths each year [1, 2]. Although the prevalence of cigarette smoking has declined among adults in the US since 1983, smoking among young adults aged 18–25 years has remained stable, with past month cigarette use rates as high as 31 % in 2013 [3]. Almost all smokers (98 %) report starting before the age of 26 years [4], and more than 2000 US youth and young adults become daily cigarette smokers each day [4, 5].

Despite comparable smoking prevalence and proportion motivated to quit, relative to other adult age groups, young adults are less likely to use interventions for smoking cessation [6]. Further, studies of tobacco use and other health behaviors have reported great challenges in recruiting young adults [7, 8]. Online smoking cessation strategies (e.g., websites designed to help people quit smoking) reach large numbers of smokers [9] but tend not to have a personalized approach to smoking cessation or to have follow-up treatment contacts [10]. Young adults are less likely to take advantage of these cessation resources, and studies of web-based smoking cessation programs have been associated with large drop-offs in engagement throughout the course of participation [11–14]. Websites directly targeted to young adults have typically focused on college students [15, 16] who are less likely to smoke than non-college bound young adults [17, 18]. There is a need to develop innovative smoking cessation interventions to engage a wide audience of young adult smokers.

Social media represents a promising strategy to deliver evidence-based smoking cessation interventions to young adults. Social media tools are widely popular among young adults (89 % of 18 to 29 year old Americans use the internet) [19] and can be harnessed to widely disseminate information about a broad range of behavioral and emotional changes including smoking cessation [20–23]. Facebook remains the most widely used social media tool by young adults in the United States. With 87 % of US online young adults having a Facebook account and 70 % of those accessing it daily [19], there is promise to use this platform to deliver public health intervention programs to young people. Previous evaluations using Facebook to change health risk behavior have shown feasibility as measured by participant’s engagement and satisfaction [24–32]. However, trials examining social media interventions have shown limited or no effects on health behavior change (e.g., physical activity) [33]. The BIO smoking cessation campaign for young adults in Canada, incorporating a website, Smartphone app and Facebook features, resulted in greater 7- and 30-day reported quit rates than referral to a Smokers’ Helpline at 3 month follow-up [34]. Research is needed to determine whether Facebook alone can be used as an intervention tool, whether abstinence can be biochemically verified, and whether abstinence rates can be maintained over 1 year.

Our group conducted a mixed-methods study to determine how young adult smokers would like to use Facebook to help change smoking behavior. About a third (31 %) of survey respondents reported they would want to quit smoking using Facebook, and interest was greater among those more motivated to quit, who had made a quit attempt in the past year, and had previously used the Internet for assistance with a quit attempt (all *p* < 0.01). In qualitative interviews, social support and convenience were identified as strengths of a Facebook intervention, while privacy was the main concern [35].

Based on this formative work, we developed the *Tobacco Status Project (TSP),* a Facebook intervention for young adult smokers combining Facebook contacts tailored to participants’ readiness to quit smoking with a 12-week cessation program consisting of 90 days of Facebook postings, weekly counseling sessions, and for those ready to quit, 7 state-of-the-art group cognitive-behavioral sessions. A feasibility trial enrolled 79 young adults who formed 7 Facebook groups [36]. Follow-up rates were 84 and 72 % at 6 and 12 months, respectively, and reported 7-day abstinence was 21 % at 6 months (9 % biochemically-verified) and 18 % at 12 months (9 % verified) ([name], [name], [name], [name]: Feasibility and quit rates of the “Tobacco Status Project”, submitted). From baseline to 12-months, there was a significant increase in the proportion prepared to quit (13 to 46 %, p < .001), 35 % reduced their cigarette consumption by 50 % or greater, and 67 % reported a 24-h quit attempt. Engagement in the intervention was high, with 92 % participation in the full 3 month intervention and 61 % commented on at least one post, with more commenting among those randomized to receive a personal monetary incentive [37]. Participants reported reading most of the Facebook posts (mean usability rating = 3.3/4) and interactions from counseling sessions (3/4), thinking about what they read (3/4) and would recommend the program to others (3.3/4). Herein, we describe a randomized controlled trial testing the efficacy of TSP against a referral control condition with 480 young adult smokers who use Facebook.

## Aims and hypotheses

### Main Aim: To evaluate the efficacy of the Facebook-based intervention for young adults in a randomized controlled trial

Hypotheses are:Participants receiving the intervention will have higher 7-day point prevalence abstinence at 3-, 6-, and 12-months follow-up compared to those in the control condition.Participants in the intervention condition will demonstrate greater reduction in cigarettes smoked and increased commitment to abstinence at 3-, 6-, and 12-months follow-up than those in the control condition.Participants in the intervention condition will be more likely to make a quit attempt during the 12-month study period compared to those in the control condition.

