### Measures

#### Primary outcome

The primary outcome biochemically-verified 7-day point prevalence abstinence at 3, 6, and 12 months. Participants reporting “no smoking, not even a puff” in the past 7 days will be coded as abstinent from cigarettes. At each follow-up assessment, participants reporting 7-day abstinence will be mailed a saliva cotinine test kit and asked to record two pictures: one giving a saliva sample, and another of the test result. Participants with a salivary cotinine level <11 ng/ml, indicating nonsmoking [50], will be considered confirmed nonsmokers. If participants indicate use of an electronic nicotine delivery-system to aid in smoking cessation, saliva cotinine and reported ENDS use will be recorded and reported separately from biochemically verified abstinence.

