### Power calculation

Previous trials of stage-based interventions for smoking cessation [53–57] and trials of Internet interventions for smokers motivated to quit [11, 58] suggest that quit rates for motivated smokers may be as high as 20 % (treatment) and 9 % (control). However, as this will be the first stage-based intervention for young adult smokers delivered over Facebook, and cessation rates in some Internet trials have been as low as 7 % point prevalence abstinence at 3 month follow-up [59], the conservative estimate of 10 % (treatment) and 5 % (control) 7-day point prevalence abstinence at 3, 6, and 12 months follow-up was made. Further, attrition in Internet cessation trials has tended to be as high as 50–75 % at 3 and 6 months follow-up [11, 12, 59]. With 50 % attrition at each time point, and at least one covariate (depending on group differences), a sample size of 480 will provide a minimal power level of .80, and a Type-I error rate of .05 to detect these cessation rates in the most conservative outcome of the study - 7-day point prevalence abstinence.

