### Data analysis

#### Primary analyses

Preliminary analyses will describe and summarize all measures and test the correlation between order of study entry and outcome rates of dropout by condition. If differences for any of these variables are noted, they will be statistically controlled as covariates in model testing. Missing data will be minimized through online assessment. When subjects do not complete online assessments, they will be re-contacted through Facebook or email to obtain missing information. For each hypothesis test, two sets of outcome analyses will be conducted - one with all participants who are maintained in the study, and another based only on biochemically verified smoking abstinence rates to allow for direct comparison of findings with the research literature.

The primary outcome of biochemically-verified 7-day abstinence will be compared between participants in the TSP and Control groups at 3- through 12-months follow up using a mixed-effects statistical model [60, 61]. The independent variables will be intervention versus the control condition, assessment point, plus covariates identified in preliminary analysis. The model will be estimated using maximum likelihood estimation.

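### The primary model as listed gives one averaged treatment effect, while the hypothesis and outcome are stated separately at 3, 6 and 12 months

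*Protocol article*

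**What the plan says.** The first hypothesis under the Main Aim reads "Participants receiving the intervention will have higher 7-day point prevalence abstinence at 3-, 6-, and 12-months follow-up compared to those in the control condition". The Primary outcome section names the same three visits and singles out none: "The primary outcome biochemically-verified 7-day point prevalence abstinence at 3, 6, and 12 months".

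Under Primary analyses, the conditions are to be compared "at 3- through 12-months follow up using a mixed-effects statistical model". The next sentence lists what enters that model: "The independent variables will be intervention versus the control condition, assessment point, plus covariates identified in preliminary analysis". No product of condition and assessment point is listed, and no contrast at an individual visit.

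The Power calculation assumes a difference that does not change over time: "the conservative estimate of 10 % (treatment) and 5 % (control) 7-day point prevalence abstinence at 3, 6, and 12 months follow-up was made".

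On durability, the Background says research is needed on "whether abstinence rates can be maintained over 1 year", and the Discussion closes by saying the trial will help to settle whether social media can serve long-term verified cessation. The intervention itself runs for 90 days.

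**The concern.** With condition and assessment point as separate terms only, the condition coefficient is a single log odds ratio shared by all three visits. The assessment term does describe change over time, but the same change in both arms. The model therefore has no parameter for a treatment difference that grows or fades.

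The hypothesis is about each visit, and treatment ends at about month 3, so roughly nine of the twelve months of follow-up are untreated. A benefit that is strong at 3 months and gone by 12 could still produce a significant averaged effect. A reader who goes from that result to the hypothesis as worded would conclude that abstinence was higher at 12 months too. What is at stake is the support for visit-specific and long-term conclusions, not the validity of the averaged test.

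**Working it through.** **Inputs.** From the Power calculation: N = 480, 10% vs 5% at every visit, 50% attrition at each visit, alpha .05, power .80. Assumed, because not stated: 1:1 allocation (240 per arm, so 120 observed per visit) and two-sided testing. The waning pattern in step 2 is invented for illustration.

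**1. What the listed model estimates.**

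- As listed: logit P(abstinent) = a + b·condition + c(visit) + covariates + person effect. The condition odds ratio is exp(b) at 3, 6 and 12 months alike.
- With the product term: logit P = a + b·condition + c(visit) + d(visit)·condition + covariates + person effect. The odds ratio at a visit is exp(b + d(visit)), so the three can differ.

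**2. Illustration.** TSP 15/10/5%, control 5/5/5%. Control odds are 0.05/0.95 = 0.0526.

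| Visit | TSP odds | Odds ratio |
|---|---|---|
| 3 months | 0.15/0.85 = 0.1765 | 3.35 |
| 6 months | 0.10/0.90 = 0.1111 | 2.11 |
| 12 months | 0.05/0.95 = 0.0526 | 1.00 |

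Averaging the proportions gives 10% vs 5%, odds ratio 0.1111/0.0526 = 2.11. Fitting the logistic model with condition and visit only to these six proportions (marginal, no person effect) gives a common odds ratio of 2.12. Its fitted 12-month rates are 6.7% vs 3.3%, although the true rates are 5% and 5%. A mixed logistic model estimates a person-specific odds ratio, so its value would differ; the constraint to one value is the same.

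**3. How often this would mislead.** Simulation of the same pattern: 2,000 runs, 120 per arm seen at all visits, within-person correlation of the yes/no outcome about 0.23 and 0.49. Tests were on the risk-difference scale, as a stand-in for the mixed logistic model.

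| Correlation | Averaged effect significant | 12-month contrast significant | Condition-by-visit test significant |
|---|---|---|---|
| 0.23 | 59% | 2% | 59% |
| 0.49 | 49% | 2% | 72% |

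The first two columns count only results favouring TSP.

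**4. Precision of a single visit at the plan's rates.** With 120 per arm and pooled rate 0.075:

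- Null SE = √(2 × 0.075 × 0.925 / 120) = 0.0340
- Alternative SE = √((0.10 × 0.90 + 0.05 × 0.95) / 120) = 0.03385
- Power = Φ((0.05 − 1.96 × 0.0340) / 0.03385) = Φ(−0.49) = 0.31

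The 95% interval is about ±1.96 × 0.03385 = ±6.6 percentage points around a 5-point difference. At Holm's first step (.05/3 = .0167, z = 2.394), power is Φ(−0.93) = 0.18. With no attrition (240 per arm) and unadjusted .05 it is 0.55.

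**5. The plan's own figure.** The Power calculation states "a sample size of 480 will provide a minimal power level of .80, and a Type-I error rate of .05". A single visit at 120 per arm gives 0.31, not .80. Pooling three visits at 50% attrition gives at most 0.72 two-sided, when visits are uncorrelated. How the .80 was obtained is a separate question, and the present point does not rest on it.

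**The case against.** Several counter-arguments have weight.

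- **The sentence lists variables, not every model term, and a journal article condenses.** Fair, and a fuller plan may contain the product term. But this is an explicit list for the primary model, and followed as written it does not match the hypothesis. The comparison from 3 through 12 months does not add an interaction.
- **An averaged effect is a legitimate primary test.** This stands. It is one test at .05, and it matches the constant rates assumed for planning. The recommended change keeps it.
- **Maintenance is not a hypothesis of the trial.** Also right: the phrase is a research need in the Background. However, the hypothesis names 12 months explicitly, and the Discussion points to long-term cessation.
- **The waning pattern has no source.** True; it shows what the model would conceal, not what is expected. The feasibility trial reported verified abstinence of 9% at both 6 and 12 months, which does not suggest fading over that interval. It was a single-arm result with no verified 3-month figure, so it says nothing about the between-arm difference.
- **Visit-specific tests are weak.** Correct: 31% power per visit, 18% at Holm's first step. That is a reason to keep them secondary and to show intervals.

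A reader might also infer that naming three visits means three primary tests, each at .05, so that the stated type I error fails. The document does not support that: Primary analyses proposes one mixed model and no separate primary test per visit.

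**Conclusion.** The point holds as a mismatch between hypothesis and model. As listed, the primary analysis validly tests a time-averaged effect but cannot show whether TSP differs from control at each of 3, 6 and 12 months, or whether a difference lasts to 12 months. In the illustration, a common odds ratio of about 2.1 coexists with a 12-month odds ratio of 1.0, and the averaged test is significant in about half or more of simulated trials (49–59%) despite no 12-month effect.

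The structural conclusion needs only the listed variables. The sizes depend on the invented waning pattern, 1:1 allocation, two-sided .05, 120 per arm observed and the correlations used. It would be too strong to say that the primary test is invalid or its error rate inflated. This should be corrected before unblinded analysis; it does not undermine the trial.

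**What to change.** 1. Add condition by assessment point to the primary mixed model.
2. Name the time-averaged condition contrast from that model as the single primary test at .05, and state its weights. Equal weights on the log odds ratios are the natural choice; in the illustration they give exp((1.210 + 0.747 + 0)/3) = 1.92, against 2.12 from the model without the product term.
3. Report the 3-, 6- and 12-month contrasts with confidence intervals as secondary results, Holm-adjusted if they are tested.
4. State that no 12-month or maintained effect will be claimed from the averaged test alone.

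The cost is one product term (two parameters) and a few sentences, with no new data. The real downside is imprecision: at the plan's rates each visit contrast has about 31% power, with an interval of about ±6.6 points around a 5-point difference. A non-significant 12-month contrast must therefore not be read as evidence that the effect has gone.

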### Secondary Aim: To evaluate effectiveness of a monetary incentive for engagement in the Tobacco Status Project intervention

Analyses will examine:Engagement by incentive group (daily, weekly, monthly, no incentive);Abstinence rates by incentive group; andEffect of engagement on abstinence

## Methods/Design

### Overview of design

This study is a randomized controlled trial (RCT) with 480 young adults age 18 to 25 recruited through Facebook (Fig. 1). Participants are randomized to one of two conditions: (1) the Tobacco Status Project motivationally-tailored smoking cessation intervention delivered through Facebook (TSP); or (2) a control condition (referral to the Smokefree.gov website). Assessments are conducted online at baseline, 3-, 6-, and 12-months follow-up. Primary outcome is biochemically-verified 7-day point prevalence abstinence from tobacco, and secondary outcomes are reduction in cigarettes smoked per week, 24 h quit attempts, and commitment to abstinence in each time period. Within the TSP group, a monetary engagement will be tested as a moderator of engagement and abstinence.

**Fig. 1 Fig1:**
[figure not shown]
Flow of participants through trial

### Inclusion criteria

Participants are required to meet the following criteria in order to be eligible for enrollment in the trial:English literate (at an 8^th^ grade reading level);age 18 to 25 years (consistent with the definition of young adulthood used by the National Survey of Drug Use and Health, and age range with the highest smoking prevalence nationally [38]);access to a digital camera that can take and send a picture (e.g., camera phone);go on Facebook “most” (≥4) days per week;≥100 cigarettes smoked in their lives; and currently smoking at least 1 cigarette per day on 3 or more days of the week. Smoking criteria are based on those used in the National Health Interview Survey and are liberal based on smoking patterns most common in young adults and to include ethnic/racial minority populations, who tend to smoke fewer cigarettes per day than Caucasians [1].

### Exclusion criteria

previous participation in the TSP feasibility trial.

### Recruitment

Figure 1 shows the flow of participants through the trial. Participants are being recruited over 16 months primarily from Facebook based on a media campaign that has been successfully employed by the team in previous online survey and interventions studies [36, 39, 40]. Facebook advertisements are targeted based on: 1) age (18 to 25); 2) location; 3) gender; 4) race/ethnicity; and 4) keywords related to tobacco use. Ads include an image and short text consistent with Facebook’s advertising guidelines. Most ads mention the study incentive. Facebook’s Ads Manager program tracks progress of all advertisements in a campaign based on budget, numbers of clicks on an ad, and likelihood of enrollment in a study. Ads include a link to the study’s independent Qualtrics website with a short description of the study and eligibility questions. If respondents are eligible, then they will be taken to the study’s informed consent page.

### Study procedure

Informed consent is obtained from all study participants in accordance with the Helsinki Declaration and approved by the UCSF Committee in Human Research (#11-06294). During the informed consent process, participants’ understanding of the information provided is assessed through a series of multiple choice questions with required responses before being able to proceed with the study. Questions are based on those used in studies with potentially vulnerable populations [41, 42]. Any wrong answers during the consent process are sent to study staff who then contact a potential participant via email or Facebook for further clarification of the consent process. Therefore, no participant will be enrolled that has not answered all consent questions correctly. Participants consenting to participate in the study are asked to verify age by sending proof through email or social media. Verified participants are emailed a baseline assessment. Those completing the baseline assessment are randomized to receive either the Tobacco Status Project (TSP) intervention of referral to the Smokefree.gov website (control).

A stratified random assignment program was developed and participants are assigned from within stratified blocks immediately after completing the baseline assessment. Participants are stratified on stage of change (precontemplation, contemplation, preparation) and smoking pattern (daily vs. non-daily), variables known to be related to outcomes and addressed by the intervention [43]. Participants in the TSP group are assigned to “secret” (private) Facebook groups based on their readiness to quit tobacco. Groups begin when there are approximately 10 participants enrolled, as that has been deemed the optimal number based on analyses of engagement in our previous work [37] ([name], [name], [name]: Smoking cessation intervention on Facebook: Which content generates the best engagement?, submitted). Participants in the control condition are given a referral to the Smokefree.gov program and are encouraged to use it as much as they would like.

Assessments occur online using the survey program Qualtrics at baseline, 3, 6, and 12 months follow-up. Participants receive their choice of gift cards in the amount of $20 per assessment, and a $20 bonus for completing all three assessments, for a total possible stipend of $100 for completing all assessments.

